### Hybrid EEG and HD-tDCS montage

2.6

A hybrid device will be employed to record EEG and deliver anodal tDCS (StarStim 32, Neuroelectrics, Spain); the stimulation/EEG sessions will be managed by the NIC2 software v2.0.11 (Neuroelectrics, Spain).

The configuration will include 8 electrodes positioned in a non-conductive neoprene cap. Direct current will be delivered using small, round gel electrodes (Ag/AgCl, 3.14 cm2), each filled with conductive electrolyte gel and positioned according to the international 10/10 EEG system. Anodal direct current delivered will be set at a total intensity of 2 mA equally distributed to the stimulation electrodes placed over F3 and T7 (1 mA each). Six return electrodes will be placed around the anodal electrodes over Fp1, FC1, F7, C3, CP5 and P7 (Figure 2) and the overall return current (−2 mA) will be equally distributed among these electrodes. This distribution of electrical current makes the minimal cathodal effects induced at the return positions not able to lead relevant changes in brain activity (Figure 2). Each stimulation session (real and sham) will last 21 min, including 30s fade-in and 30s fade-off periods. In the sham stimulation, the montage will be identical to that of the real stimulation, but the real anodal stimulation will be delivered for a duration of 30 s only. This montage will reproduce the same itching sensation associated with real stimulation thus allowing effective blinding (34).

**Figure 2 fig2:**
[figure not shown]
Montage template and current distribution maps. **(A)** EEG and tDCS electrodes’ placement template; anodes placed over F3 and T7, return current distributed over the remaining electrodes; **(B)** current diffusion map of the left hemisphere; **(C)** current diffusion map of the right hemisphere.

The same electrodes used to deliver brain stimulation will serve for the EEG recordings derived before and after the stimulation sessions (sessions 1, 8, 9 and 16; Figure 1). The common mode sense (CMS) and the driven right leg (DLR) connections will be positioned on the right earlobe as electrical reference. Electrodes impedance for brain stimulation and recording will be checked before starting the session and monitored through its duration to ensure impedance values lower than 10 kΩ. Each EEG recording will last 5 min.

### Preprocessing of EEG signal

2.7

Preprocessing of EEG data will be conducted with the open-source toolbox EEGLAB (35) in the MATLAB environment (MathWorks Inc., 2022, version 2014b). Data will be sampled at a frequency of 250 Hz and band-pass filtered with a passband between 0.1 Hz and 45 Hz to eliminate motion artefacts and physiological artefacts. Then, each EEG trace will be visually inspected to remove eyeblinks and saccades signals. The power spectral density (PSD) will be then calculated with MATLAB (MathWorks Inc., 2022, v. 2014b) for the alpha, beta, theta and gamma frequency bands, separately for each participant and session. Subsequently, a root square or a logarithmic transformation will be performed where necessary to normalize data (36).

### Sample size justification and statistics

2.8

The final sample size of 60 participants is estimated based on a sample size calculation on G*Power (v. 3.1.9.7) suggesting a sample size of at least 48 participants to compare the two groups along three-time points with an effect size = 0.25, power = 0.80, *ε* = 0.75, and a Bonferroni-adjusted *α* = 0.0125 (0.05/4 primary cognitive outcomes see below) and considering a dropout rate up to 30% from previous studies (37, 38).

Demographic data will be reported using descriptive statistics. Primary outcomes will be the measures of cognitive (MOCA, FAB, FCSRT, Stoop scores) and affective (GDS scores) functioning, while independence in daily living (ADL and IADL scores) and EEG parameters will be considered as secondary outcomes. Intention-To-Treat (ITT) analyses (39), which includes all randomized participants in the groups assigned, regardless of their adherence with the entry criteria, will be adopted. ITT analysis admits noncompliance and protocol deviations and gives an unbiased estimate of the intervention effect. Missing data will be dealt with by using a mixed-effect model approach which accommodates missing data under the missing-at-random assumption (40). To assess the effect of the intervention on multiple dependent variables simultaneously, repeated-measures analyses of variance (ANOVAs) will be conducted on the primary outcomes and secondary outcomes separately with the factors Group (G1 vs. G2) and Time (T1-T3). Moreover, multiple regression models will be used to identify the factors associated with the treatment outcome, considering gender, age, education, CRS scores, and EEG power spectrum at baseline as predictors and post intervention measures of general cognitive functioning (MOCA and FAB) and functional independence measures as criteria.

To assess possible sequence or carryover effects, an exploratory comparison of treatment effects between the two randomization arms (sham first over real vs. real first over sham) will be performed.

Statistical analysis will be performed using IBM® SPSS® Advanced Statistics and R package (R Foundation). Statistical significance will be set at *p* < 0.05.

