To achieve these purposes the present study protocol will adopt a double-blinded sham-controlled crossover experimental design in patients with MCI and early stages of dementia, combining brain stimulation and electrophysiological recording. The primary outcomes will be global cognitive functioning, anterograde verbal episodic memory and executive functions as well as affective symptoms. Secondary outcomes will be the level of functional independence in daily living and electrophysiological measures. Based on the available literature we expected to observe an effect of brain stimulation on cognitive and affective functions (7, 11). Moreover, we expect the use of EEG recording being able to provide findings useful to distinguish good and bad responders to the treatment based on individual analysis (9, 10). Finally, we hypothesize that demographic factors can modulate the possible outcomes, thus contributing to identify the patients most suitable for such intervention (3, 7).

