### Neuropsychological assessment

2.5

A brief battery of neuropsychological tests will be used to monitor cognitive functions, affective symptoms and independence in the participants involved in the treatment (T1, T2, T3; Figure 1).

*Montreal Cognitive Assessment* [MOCA; (26)]. MOCA is a brief neuropsychological tool for screening global cognitive functioning specifically designed for MCI and early stages of dementia. The test includes 8 sub-tests assessing: executive functions, visuo-spatial abilities, naming, short-term and long-term episodic memory, attention, lexical access, abstraction, spatial and temporal orientation. The test provides a maximum score of 30; the higher the score, the higher the level of global cognitive efficiency.

*Frontal Assessment Battery* [FAB; (27)]. FAB is a screening neuropsychological battery including 6 sub-tests for evaluation of executive functioning: classification, mental flexibility, motor programming, sensibility to interference, inhibitory control and environmental autonomy. The total score is up to 18; the higher the score, the higher the level of executive functioning.

*Free and Cued Selective Reminding Test* [FCSRT; (28)]. FCSRT is designed to assess episodic memory domain. The test entails learning 12 pictorial stimuli (6 living and 6 non-living), followed by free and cued recall tasks. It assesses immediate and delayed recall, both free and cued, as well as recognition ability. The FCSRT is sensitive to memory impairments where recall does not significantly improve with cues, rendering it a valuable tool for identifying early signs of the disease. The test provides separate scores for free, cued and total *immediate* recall (maximum score 36), and scores for free, cued and total *delayed* recall (maximum score 12). For these measures the higher the scores, the higher the memory performance. Moreover, the FCRS provides a cue-sensitivity index (range 0–1) representing the extent of facilitation using the semantic cues in memory recall.

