*Stroop Color and Word Test* (29). The Stroop Test aims at assessing the ability to inhibit cognitive interference. Participants are presented with three tables and are required to respond as quickly as possible. Two tables represent the ‘congruent condition’: in the former participants have to read color names (hereafter referred to as color words) printed in black ink, and in the latter, they are required to name color patches. Conversely, in the third table, the so-called color-word condition, the color words are printed in an incongruent color (for example, the word ‘red’ is printed in green ink), and participants have to name the color of the ink instead of reading the word. The test provides two measures, i.e., overall number of errors and time to complete the test, with higher scores indicating worse performance.

*Geriatric Depression Scale* [GDS; (30)]. GDS is a specific evaluation tool to diagnose severity of depression symptoms in older adults. This questionnaire, including 30 items, is designed for the older person and defines his/her degree of satisfaction, quality of life, and feelings. The maximum score is 30 with higher scores indicating higher levels of depression.

*Cognitive Reserve Scale* [(31); CRS; (32)]. The Italian version of the CRS is a self-rated questionnaire evaluating the engagement of a person in several activities, i.e., daily activities, training or information, hobbies, and social life. The CRS allows to assess CR in three life stages: young adulthood (18–35 years), middle adulthood (36–64 years), and late adulthood (≥65 years). According to their ages, participants have to complete the questionnaire once, twice or three times referring to the main activities during young adulthood, middle adulthood and late adulthood. Each of the 24 items is scored on a Likert scale based on the frequency each activity is performed during a week (0 = never; 4 = twice or three-time a week). The total score of the CRS is obtained by the sum of each item (maximum score 96). The higher the score, the higher the level of CR. Depending on the age of participants the scores is averaged for each of the age period.

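### The trial is sized at a Bonferroni level of 0.0125 for four cognitive outcomes, but five instruments are primary and the only analysis level stated is an unqualified p < 0.05

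*Protocol article*

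**What the plan says.** All the main statements stand in section 2.8 of the protocol article (Sample size justification and statistics).

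- **Planning level.** The minimum of 48 participants is computed at an alpha of "0.0125 (0.05/4 primary cognitive outcomes see below"), with "effect size = 0.25, power = 0.80", a nonsphericity correction of 0.75, two groups and three time points.
- **Primary outcomes.** "Primary outcomes will be the measures of cognitive (MOCA, FAB, FCSRT, Stoop scores) and affective (GDS scores) functioning". That is four cognitive instruments and one affective instrument. The Background section also counts affective symptoms as primary: "The primary outcomes will be global cognitive functioning, anterograde verbal episodic memory and executive functions as well as affective symptoms".
- **Analysis.** Repeated-measures ANOVAs with Group and Time are named for the primary and secondary outcomes. No multivariate test, hierarchy or gatekeeping is named.
- **Decision level.** The section ends: "Statistical significance will be set at *p* < 0.05". The figure 0.0125 does not appear again after the sample size sentence.

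Section 2.5 (Neuropsychological assessment) describes several outputs for two of the instruments. FCSRT gives free, cued and total scores for immediate and for delayed recall, and in addition "the FCRS provides a cue-sensitivity index". For Stroop, "The test provides two measures, i.e., overall number of errors and time to complete the test".

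**The concern.** A Bonferroni-adjusted alpha in a sample size calculation only has meaning if the same level is used to judge the results. Here the sample size rests on 0.0125, while the only level given for the analysis is 0.05. A result such as p = 0.03 on one primary instrument would count as a success under the closing sentence and as a failure under the planning level. The text does not settle which applies, and the question would then be answered with the data in view.

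The divisor is a second, smaller matter. It counts the cognitive primaries only, so GDS has primary status without a share of the error budget. At stake is the chance of declaring the intervention effective on at least one primary outcome when it has no effect on any of them.

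**Working it through.** **Inputs.** From section 2.8: alpha 0.0125, effect size 0.25 (read as Cohen's f), power 0.80, ε = 0.75, k = 2 groups, m = 3 time points, N = 48, five primary instruments, closing level 0.05. From section 2.2 (Participants): recruitment continues until at least 60 participants complete. Assumed, because the article does not give it: correlation among repeated measures ρ = 0.5, with 0.3 to 0.7 shown as a range. One test (the Group × Time interaction) is counted per instrument.

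**1. The plan's own figures.** 0.05 / 4 = 0.0125, as stated. For the within-between interaction:

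- λ = f² × N × m × ε / (1 − ρ) = 0.0625 × 48 × 3 × 0.75 / 0.5 = 13.5
- df1 = (k − 1)(m − 1)ε = 1 × 2 × 0.75 = 1.5
- df2 = (N − k)(m − 1)ε = 46 × 2 × 0.75 = 69

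The noncentral F distribution then gives power 0.816 at alpha 0.0125. The smallest N in equal groups reaching 0.80 is 48, so the stated figure reproduces under ρ = 0.5. At an unadjusted 0.05, 34 would be enough. With this ρ, the 48 does rest on the adjusted level.

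**2. Family-wise error if the closing sentence is followed (0.05 on each test).**

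- Four independent tests: 1 − 0.95⁴ = 18.5%
- Five independent tests: 1 − 0.95⁵ = 22.6%
- Five tests, simulated with equal correlation between two-sided tests: 20.8% at 0.3, 18.4% at 0.5, 14.8% at 0.7

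**3. Family-wise error if 0.0125 is used on all five.**

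- Bonferroni bound: 5 × 0.0125 = 6.25%
- Independent tests: 1 − 0.9875⁵ = 6.1%
- Same simulation: 5.8%, 5.2% and 4.3% at correlations of 0.3, 0.5 and 0.7

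**4. Effect of a divisor of five on power.** 0.05 / 5 = 0.01. The same formula with ρ = 0.5 gives:

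| N | power at 0.0125 | power at 0.01 |
|---|---|---|
| 48 | 0.816 | 0.793 |
| 50 | 0.836 | 0.814 |
| 60 | 0.910 | 0.896 |

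The minimum N rises from 48 to 50. The assumption about ρ matters far more than the divisor: at N = 48 and alpha 0.01, power is 0.61 for ρ = 0.3 and 0.97 for ρ = 0.7. With 60 participants and ρ = 0.3 (λ = 12.05, df2 = 87), power is 0.77 at 0.0125 and 0.74 at 0.01. Any shortfall there comes from ρ and exists at the plan's own alpha as well.

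**The case against.** The best defence is that the closing sentence is a general one. It follows the software statement, and it must also cover the secondary, regression and exploratory analyses. It may mean the overall level from which 0.05/4 was derived, or the threshold for already adjusted p-values. The divisor is also right for its own label: four cognitive outcomes are announced and exactly four cognitive instruments are named, so correcting within the cognitive domain could have been intended. The Background names four outcome domains, one of them affective, which offers another route to the number four.

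These readings are possible, but none is written down. Section 2.8 never says that 0.0125, or any adjustment, applies to the primary tests. Its divisor is tied expressly to cognitive outcomes, so the four-domain reading does not fit it. What does stand is that the four-versus-five mismatch is close to immaterial by itself.

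A reader might be tempted to go further in three ways that the article does not support.

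- **Twelve primary tests.** Counting seven FCSRT scores, two Stroop scores and one each for MOCA, FAB and GDS gives 12, and 1 − 0.95¹² = 46.0% under independence. But section 2.5 only describes what the instruments produce, and the divisor of four implies one outcome per instrument. Naming the score is commonly left to the full protocol or SAP, neither of which is shown. Twelve is an upper limit, not a stated plan. Independence is also implausible among recall scores from the same items; correlations of 0.3 to 0.7 would bring the 46% down to about 40% to 23%.
- **Scores chosen after the data are seen.** Nothing in the article says so.
- **The trial is underpowered for five primaries.** The loss at N = 48 is 0.816 − 0.793 = 0.023, small beside the uncertainty from the unstated correlation.

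**Conclusion.** The point holds as a contradiction within section 2.8. The trial is planned at 0.0125, five instruments are primary, and the level stated for the analysis is 0.05 with no adjustment attached. An unseen SAP could say which level is used, but the published section would still carry both.

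Taken literally, the text allows a family-wise error of about 15% to 23% across five primary tests. The upper end assumes independence and the lower end a correlation of 0.7 between tests. If 0.0125 was meant to govern all five, the excess over 5% is at most 1.25 percentage points, and the remaining fault is that this was not said and GDS was not counted. The literal reading is not certain to be the intended one, so the conclusion is that the level governing the primary tests is unresolved, not that the error rate will necessarily be inflated. The error figures count one test per instrument; the power figures rest on ρ = 0.5.

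**What to change.** Change the wording of section 2.8 before any data are unblinded:

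1. State that there are five primary outcomes (MOCA, FAB, FCSRT, Stroop, GDS), each represented by one score, and name that score here or in the SAP.
2. State that they are tested with family-wise error controlled at 0.05, for example by Holm's procedure with a first step of 0.05/5 = 0.01.
3. Limit the closing p < 0.05 to secondary and exploratory analyses.
4. Restate the planning alpha as 0.01, and give the repeated-measures correlation used in the calculation.

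If the sponsor prefers to keep GDS outside the corrected family, it should say so and give GDS a status that matches.

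The cost is editorial. Under ρ = 0.5 the minimum becomes 50 instead of 48, within the planned 60 completers, where power is about 0.90. Holm is never less powerful than Bonferroni at 0.01, so these power figures are conservative for it. The change itself calls for no additional recruitment.

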**Method:**

Sixty patients with MCI and early-stage dementia will be enrolled in a crossover double-blind randomized controlled trial utilizing an integrated intervention combining conventional cognitive treatment with multifocal brain stimulation and electrophysiological recordings. A battery of standardized neuropsychological tests will be employed at several time points to monitor changes, and inferential statistics will identify the changes specifically associated with the intervention. Regression analyses will be performed to ascertain the extent to which education and cognitive reserve scores may influence intervention outcomes. Analysis of electrophysiological data will contribute characterizing responders to treatment.

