### Participants

2.2

The recruitment centers for the study will be “Alma Mater Camaldoli Hospital” (Naples) and the Neuropsychological Testing Service of the Department of Psychology of University of Campania “Luigi Vanvitelli” (Caserta) in Italy. All participants consecutively admitted to the two centers will be screened for study participation. Data collection will be terminated when at least 60 participants will complete the whole intervention. Inclusion criteria are: (i) age between 55 and 85 years, and (ii) diagnosis of minor neurocognitive disorder, or major neurocognitive disorder with mild severity, according to Diagnostic and Statistical Manual of Mental Disorders [DSM-5; (20)] with a Clinical Dementia Rating Scale (CDR) of 0.05 or 1 (21), (iii) right handedness. The diagnosis will be made by expert neurologists and neuropsychologists. Exclusion criteria are: (i) brain events with an acute aetiology (stroke, traumatic brain injury, neoplastic ablation), (ii) psychiatric disorders (schizophrenia, psychosis, bipolar disorder) and assumption of psychotropic drugs, (iii) diagnosis of moderate or severe major neurocognitive disorders [DSM-5; (20)] with CDR scores equal or above 2 (21), (iv) any condition which might even hypothetically interfere with electrophysiological recording and neurostimulation (metallic implants in the brain, cochlear implant, pacemakers, epilepsy) (22, 23).

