However, as discussed by recent studies in the field of closed-loop and brain state-dependent stimulation (50, 51), implementing truly individualized closed-loop therapeutic systems capable of reliably extracting complex brain states in real-time and identifying suitable biomarkers is currently a proof of concept and faces significant engineering and neurophysiological challenges. Moreover, strong and replicable evidence regarding the safe and effective modulation of cognitive and affective functions would be needed in healthy samples before these advanced prototypical approaches can be widely applied for rehabilitative purposes. The understanding of how our intervention affects brain oscillations seems to be a necessary step towards informing the development of future, potentially more personalized and state-dependent stimulation approaches in clinical populations.

It is possible that certain issues may impede the completion of the study protocol. A preliminary issue pertains to the participation of patients in the study, as some may prematurely withdraw from the study, thus failing to complete the full intervention program. This will be addressed through the provision of a comprehensive presentation of the study procedures and features to patients and their family members prior inclusion in the study; moreover, we will recruit a percentage of 25–30% more than the minimum sample size to ensure sufficient power to the analyses. A second issue concerns the multicenter nature of the study, which may necessitate the use of procedures that differ slightly from those employed at the other participating institution. To ensure the reliability and standardization of data acquisition and analysis processes, the experimenters involved in data acquisition at each study site will receive training and participate in regular peer-to-peer and supervision meetings. Lastly, a prompt evaluation of contraindications to brain stimulation by a physician with expertise in this field will prevent adverse effects and premature cessation of the intervention.

In conclusion, the study protocol described here responds to the new challenges posed by the ageing population, by devising an integrated rehabilitation treatment and by assessing multiple factors associated with its efficacy. Addressing these emerging issues will contribute to tackle a fundamental social problem, and to enhance quality of life of patients and their caregivers (52).

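### The target of 60 does not keep the calculated 48 at the stated 30% dropout, and the protocol does not settle whether 60 means enrolled or completed

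*Protocol article*

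**What the plan says.** The protocol article gives the size of the trial in four places.

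- **Abstract, Method:** "Sixty patients with MCI and early-stage dementia will be enrolled in a crossover double-blind randomized controlled trial".
- **Section 2.2, Participants:** "Data collection will be terminated when at least 60 participants will complete the whole intervention".
- **Section 2.8, Sample size justification and statistics:** "The final sample size of 60 participants is estimated based on a sample size calculation on G*Power", the calculation itself "suggesting a sample size of at least 48 participants to compare the two groups along three-time points", with "effect size = 0.25, power = 0.80", a nonsphericity correction of 0.75 and an alpha of 0.0125. The step from 48 to 60 is explained only by "considering a dropout rate up to 30% from previous studies".
- **Section 3, Discussion:** to guard against withdrawals, "we will recruit a percentage of 25–30% more than the minimum sample size".

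Section 2.8 also specifies an intention-to-treat analysis of everyone randomised, with a mixed-effects model for missing data under a missing-at-random assumption.

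**The concern.** There are two separate problems, and no single reading of 60 removes both.

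The first is the dropout allowance. A sample meant to withstand losses of up to 30% should still hold the calculated minimum when 30% are lost. Sixty randomised does not. The Discussion points to the likely cause: a percentage was added to the minimum, where the calculation should divide the minimum by the proportion retained.

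The second is what 60 counts. The Abstract uses it for enrolment; section 2.2 uses it for completers. With any dropout these are different trials. Two centres working from this document could stop at 60 randomised or continue to somewhere near 86, and the power of the trial differs accordingly.

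**Working it through.** **Inputs, all from section 2.8 unless noted.** Minimum N = 48; final N = 60; effect size f = 0.25; power 0.80; epsilon = 0.75; alpha = 0.0125; k = 2 groups; m = 3 time points; dropout d up to 0.30. The mark-up of 25–30% is from section 3. The correlation between visits (rho) is not stated. I assume 0.5 and show the range.

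**Step 1. Reproduce the 48.** For the group-by-time interaction in a repeated-measures ANOVA (noncentral F):

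- lambda = f² × N × m × epsilon / (1 − rho)
- df1 = (k − 1)(m − 1) × epsilon = 1 × 2 × 0.75 = 1.5
- df2 = (N − k)(m − 1) × epsilon

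At N = 48: lambda = 0.0625 × 48 × 3 × 0.75 / 0.5 = 13.5, df2 = 46 × 1.5 = 69, power 0.816. The smallest N reaching 0.80 is 47 (power 0.805), or 48 with equal groups. The stated minimum is reproduced.

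**Step 2. Apply the dropout.**

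- 60 × (1 − 0.30) = 42, which is below 48.
- Largest dropout at which 60 still leaves 48: 1 − 48/60 = 20%.
- Number needed to keep 48 after 30% loss: 48/0.70 = 68.6, so 69, or 70 with equal groups.
- Additive mark-up: 48 × 1.25 = 60 exactly; 48 × 1.30 = 62.4. The first product probably explains the 60, but the document does not write it out, so this is an inference.

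The comparison of 42 with 48 needs no assumption about the correlation.

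**Step 3. Compare the two meanings of 60.** Power is completers-only, with rho = 0.5.

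| Meaning of 60 | Dropout | Randomised | Completers | lambda | df2 | Power |
|---|---|---|---|---|---|---|
| Randomised | 20% | 60 | 48 | 13.5 | 69 | 0.816 |
| Randomised | 25% | 60 | 45 | 12.7 | 64.5 | 0.783 |
| Randomised | 30% | 60 | 42 | 11.8 | 60 | 0.745 |
| Completers | 30% | 60/0.70 = 85.7, so 86 | 60 | 16.9 | 87 | 0.910 |

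**Step 4. Sensitivity to the unstated correlation.** With 42 completers, power is 0.645 at rho = 0.4, 0.745 at 0.5 and 0.852 at 0.6. The minimum N would be 56 at 0.4 and 38 at 0.6, so of these three values only 0.5 reproduces the stated 48.

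**The case against.** The strongest reply is that section 2.2 is the only explicit stopping rule in the Method section, and that it protects the power: with 60 completers the minimum of 48 is exceeded and power is about 0.91. This stands. A reader might infer from the 42 that the trial is underpowered, but the documents support that only if 60 is the number randomised. Even so, the completer reading does not rescue the text. The Abstract's enrolment figure would then be wrong, the mark-up in the Discussion would not describe the recruitment, and the dropout clause in section 2.8 would not explain the 60.

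It is also fair to say that 30% is an upper limit, and that the planned mixed model uses the visits that dropouts did attend. Someone who leaves after T2 still contributes T1 and T2. Both points stand, so 0.745 is a floor and not an expected value. They do not repair the justification, since an allowance for losses up to 30% must hold at 30%, and even at 25% only 45 complete.

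A reader might further infer that a completer-based stopping rule is incompatible with intention-to-treat. It is not. The rule decides when recruitment ends; intention-to-treat decides who is analysed. Section 2.11 also says that withdrawn participants' data will be reported.

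**Conclusion.** The sample-size justification is wrong as written, and the recruitment target is contradictory. Sixty randomised keeps 48 participants up to 20% dropout, not 30%. Sixty enrolled and 60 completed agree only if nobody drops out, which sections 2.8 and 3 both plan against.

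The effect on power is conditional. If 60 means randomised, completers-only power at 30% dropout is about 0.75, roughly five percentage points below nominal. This rests on a correlation of 0.5, which is not stated but reproduces the 48; at 0.6 it would be about 0.85. If 60 means completers, power is about 0.91 on the same assumption and there is no shortfall. The documents do not show which is intended, so underpowering cannot be asserted outright.

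This should be fixed, but it is a matter of stated figures. The calculated minimum reproduces, and the design, outcomes and analysis method are unaffected.

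**What to change.** State one target and make the Abstract and sections 2.2, 2.8 and 3 agree with it. Either of the following would do.

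- **(a) 60 is the number randomised.** Suggested text for section 2.8: *60 participants will be randomised; this retains 48 with up to 20% dropout. At 30% dropout, 42 complete and completers-only power is about 0.75, assuming a correlation of 0.5 between visits.* Change the stopping rule in section 2.2 to match, and replace the mark-up in section 3 with the same statement.
- **(b) 60 is the number of completers.** Keep the rule in section 2.2. Correct the Abstract and the dropout text in sections 2.8 and 3, and state the expected number randomised (about 86 at 30% dropout) and the power of about 0.91, with the correlation assumed.

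Whichever is chosen, dropout should be allowed for by dividing by the proportion retained.

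Both are text corrections. Under (a), the price is a less favourable dropout tolerance, or power, than the article now implies. Under (b), it is an openly larger recruitment commitment than the Abstract states.
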